**Clinical procedures**					
Demographics		X			
Brief medical history		X			
M.I.N.I		X			
Maudsley staging method		X			
Neuroimaging		X			
Blood sample		X			
MADRS		X	X	X	X
**Disclosure of allocation**					X
**Questionnaires**					
Beck Depression Inventory-II		X		X	X
Beck Anxiety Inventory		X		X	X
Pittsburgh Sleep Quality Index		X		X	X
WHO- five Well-Being Index		X		X	X
WHO QOL BREF		X		X	X
BRIEF-A		X		X	X
**Cognitive assessment**		X		X	

*Abbreviations*: *M.I.N.I *Mini International Neuropsychiatric Interview, *WHO* World Health Organization, *QOL* Quality of life, *BREF* brief version, *MADRS* Montgomery and Asberg Depression Rating Scale, *BRIEF-A* Behavior Rating Inventory of Executive Functions—Adult version

^a^Additional safety checks are performed prior to each stimulation

The following variables are documented during the baseline visit only: sociodemographic (age, gender, laterality, years of education, professional and marital status) and medical history (length of illness, duration of current episode, number of previous episodes, psychiatric and addictive comorbidities, somatic history, treatments prescribed, degree of therapeutic resistance according to the Maudsley staging method (MSM) [38], family history of depression). Cerebral MRI (including structural and rs-fMRI) will be performed in a Siemens Biograph molecular MR system. A blood sample is required for genetic analysis of polymorphisms for BDNF, 5-HTTLPR and 5-HT1A.

The following variables are evaluated at both baseline and the end of iTBS or sham stimulation: intensity of depression symptoms according to the MADRS and the BDI-II [33, 34]. Anxiety will be assessed using the Beck Anxiety Inventory (BAI) [39]. Functional status, health-related quality of life and well-being will be measured with the World Health Organization Quality Of Life Brief Version(WHOQOL-BREF) [40] and the World Health Organization Well-Being Index [41]. Sleep will be measured with the Pittsburgh Sleep Quality Index [42]. Cognitive performance will be assessed using validated neuropsychological tests with published normative data. Subtests from the Wechsler Adult Intelligence Scale-IV [43] will be used for the estimation of general verbal capacity (similarities subtest) and working memory (digit span subtest). Subtests from the California Verbal Learning Test II short form will be used to measure verbal memory [44], and the Rey-Complex Figure Test will be used as a measure of visual memory [45]. Aspects of executive functions will be assessed with selected subtests from the Colour-Word Interference Test, the Verbal Fluency Test and the Trail Making Test, all from the Delis Kaplan Executive Functioning System [46], and with the Wisconsin Card Sorting Test [47]. A computerized N-back task [48] will be used to measure reaction time, attention and working memory. The Behaviour Rating Inventory of Executive Functions-Adult version (BRIEF-A) will be used to assess patient-reported dysexecutive problems in everyday life [49].

### Primary outcome variables

The primary outcome variable is the change in the level of depressive symptoms measured with the clinician-rated MADRS [33] from baseline to after 10 stimulations.

Change in depression symptoms will also be assessed with the self-assessment form BDI-II [34]. The main outcome will be reported as continuous changes in depression scores.

### Secondary outcome variables and covariates

Secondary outcome variables are changes in anxiety, executive functions and quality of life from baseline to after the 10th stimulation. Additionally, the stability of these measures at the last follow-up is secondary outcomes. Genetic and cerebral MRI results obtained at baseline are used only as covariates. Other covariates are participant characteristics (age, sex) and depression characteristics (treatment refractoriness, symptom severity).

### Randomization, stratification, allocation and blinding

The RCT will be run with an allocation ratio of 1:1 to the two groups (iTBS and sham). We expect a 1:1 ratio of males to females since the groups will be stratified by gender in the randomization. The randomization will be performed in MATLAB (https://se.mathworks.com/products/MATLAB.html), with the “randperm” command that performs randomization in four permuted blocks to groups and gender in a single operation. The a priori randomization procedure in MATLAB will be performed by a research assistant prior to the start of the study. This research assistant is not involved in the data collection.

The research assistant will produce numbered coloured envelopes (e.g. pink = female, blue = male), each containing a number indicating the type of coil to be used (e.g. 1 = active, 2 = sham). The staff member who performs the stimulation procedure will open the envelope. The staff members who provide iTBS will not assess the patient. Clinicians who assess the patients will not be aware of the treatment group. Thus, neither the clinician who assesses the patient nor the patient will know which treatment is provided. A study identification code will be allocated to each participant upon entry. Their name or national identity number will not appear in the research data collected. Four weeks after the last stimulation day, treatment allocation will be disclosed to the patient.

### Sample size calculation

A meta-analysis [1] reported a large effect size (Hedges’ *g*) of 1.0 favouring iTBS over sham stimulation for the reduction of depressive symptoms in major depression. Hence, using sample size calculations in GPower [50] with an estimate of a large effect size in a repeated analysis of variance (ANOVA) analysis, two groups, alpha = 0.05 and power = 0.9, the required sample size is 68, 34 in each group. The critical *F* value for the repeated analysis (pre-post) is 3.99. A study by Li et al. [11] reported a mean change after 10 treatment sessions in the iTBS group of − 42% and − 17% in the sham group and a standard deviation (SD) of 3.9. By assuming a mean baseline MADRS score of 22 in each group in the present study, the expected mean posttreatment MADRS score in each group will be 13 (active) and 18 (sham). With the two groups, alpha = 0.05, a pooled SD of 6, and power = 0.9, the required sample size is 46, 23 in each group to obtain a significant group difference in a two-tailed *t*-test. When using the same numbers for power, alpha and effect size, analyses of single means with ANCOVA-like analyses with fixed effects, main effects and interactions assuming 2 groups and 3 covariates will require group sizes of 43, e.g. 86 patients in total (critical *F* = 2.33) with equal group sizes. The analyses of repeated measures will be performed with linear mixed models (LMMs), as it manages random missing data better than repeated ANOVA. Otherwise, the sample size estimation is comparable to repeated ANOVAs due to similar residual covariance matrix assumptions [51]. There is limited information about drop-out rates for iTBS, but a meta-analysis on rTMS [52] found the mean drop-out rate to be between 7 and 8%. Thus, assuming a total drop-out of 10% in each group, the present study must recruit a total of 96 patients. Based on data from Blumberger et al. [4], we estimate a mean decrease of approximately 43% in depressive symptoms over a 2-week treatment course in those receiving iTBS. A 10-day treatment period has approximately 43% in depressive symptoms over a 2-week treatment course in those receiving iTBS. A 10-day treatment period has previously been used in RCTs, with significant differences between the iTBS condition and the sham/placebo condition [11, 53].

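### The ANCOVA total of 86 that sets the target of 96 cannot share its effect size with the other two totals, and its critical F of 2.33 belongs to an undefined 5-df test

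*Protocol article*

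**What the plan says.** The protocol article, under Sample size calculation, gives three totals, all at alpha 0.05 and power 0.90.

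- **68.** A meta-analytic Hedges' g "of 1.0 favouring iTBS over sham stimulation" is cited, and the calculation is then made "with an estimate of a large effect size in a repeated analysis of variance (ANOVA) analysis". The result is "two groups, alpha = 0.05 and power = 0.9, the required sample size is 68, 34 in each group", with a critical F of 3.99.
- **46.** Changes of −42% and −17% are applied to a baseline MADRS of 22, and the section concludes that "the expected mean posttreatment MADRS score in each group will be 13 (active) and 18 (sham"). With a pooled SD of 6, 23 per group are said to be enough "to obtain a significant group difference in a two-tailed" t-test.
- **86.** The next sentence opens "When using the same numbers for power, alpha and effect size" and turns to an ANCOVA covering main effects and interactions. It states that "assuming 2 groups and 3 covariates will require group sizes of 43, e.g. 86 patients in total", with a critical F of 2.33.

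The section then says that, "assuming a total drop-out of 10% in each group, the present study must recruit a total of 96 patients". The numerator degrees of freedom, the effect tested and the value of f behind the 86 are not given.

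**The concern.** The 86 is the figure that governs the size of the trial: 86/0.9 = 95.6, rounded up to 96. The other two totals would lead to about 76 (68/0.9) and 52 (46/0.9). A reader should therefore be able to rebuild 86 from the inputs that the section says it shares with its neighbours.

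Two things stand in the way. The critical F is far below that of a two-group comparison, so the 90% power belongs to some other test. And the three totals do not move together as they should if one effect size ran through them. What is at stake is whether the stated justification for 96 can be verified, and what the 90% power refers to.

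**Working it through.** **Inputs** (all from Sample size calculation): alpha 0.05, power 0.90, 2 groups, 3 covariates, equal group sizes, baseline 22, changes −42% and −17%, expected means 13 and 18, SD 6, g = 1.0. The value f = 0.40 for a large effect is inferred, because it reproduces the stated 68.

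**Formulas.** For two equal groups f = d/2. For the ANCOVA, noncentrality λ = f²N and denominator df = N − 2 − 3. Power is the upper tail of the noncentral F beyond the 5% critical value.

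**Step 1: which test has a critical F of 2.33?** At N = 86 the denominator df is 81. The 5% critical F is then:

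| Numerator df | 1 | 2 | 3 | 4 | 5 | 6 | 7 |
|---|---|---|---|---|---|---|---|
| Critical F | 3.96 | 3.11 | 2.72 | 2.48 | 2.33 | 2.21 | 2.12 |

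Only 5 df gives 2.33. Five does not follow from 2 groups and 3 covariates: the three interactions alone give 3 df, group plus three interactions gives 4, and adding the three covariate main effects gives 7. The 3.99 quoted for the repeated analysis is a 1-df value: F(1, 66) = 3.99.

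**Step 2: the candidate effect sizes.**

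- Large effect: f = 0.40.
- Printed means: (18 − 13)/6 = 0.833, f = 0.417.
- Unrounded percentages: 22 × (0.42 − 0.17) = 5.5 points; 5.5/6 = 0.917, f = 0.458.
- Meta-analysis: g = 1.0, f = 0.50.

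**Step 3: total N for 90% power, and power at N = 86.**

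| Effect | Two-group test, no covariates | ANCOVA, 1 df | ANCOVA, 5 df | Power at 86, 1 df | Power at 86, 5 df |
|---|---|---|---|---|---|
| f = 0.40 | **68** | 68 | 109 | 95.6% | 80.1% |
| 5/6 | 64 | 63 | 101 | 96.8% | 83.7% |
| 5.5/6 | 54 | 53 | **85 (86 with equal groups)** | 98.7% | 90.8% |
| g = 1.0 | **46** | 45 | 72 | 99.6% | 95.3% |

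The plan's three totals (bold) all reproduce, but each on a different row. The 86 reproduces together with its critical F: at f = 0.458 and 5 df, N = 85 has power 0.904, and N = 86 has power 0.908 with critical F 2.327.

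**Step 4: can one effect size give all three?** A t-test total of 46 at 90% power needs d between about 0.98 and 1.00. At that effect the 5-df ANCOVA needs 72 to 75. A 5-df total of 85 to 86 needs f of about 0.453 to 0.458. With 23 per arm, the t-test has 78.9% power at 5/6 and 86.0% at 5.5/6. The cited SD of 3.9 does not help: with it, the 5-df ANCOVA needs 46 for 5 points or 39 for 5.5 points.

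**Step 5: what 86 gives for the primary contrast.** With 1 df, power for 5 points and SD 6 is 96.8%. The f detectable with 90% power is 0.354, so d = 0.708, and 0.708 × 6 is about 4.2 points.

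**The case against.** The best defence is that 86 and 2.33 do come out together from figures in the section. The −42% and −17% of 22 differ by 5.5 points; with SD 6 and 5 df this gives 85, or 86 with equal groups. A reader might infer from the printed means that no stated input yields 86. The documents do not support that, and this part of the defence stands. It does not rescue the claim of a shared effect size, because 5.5/6 needs 54 patients in the t-test and not 46, and because the section prints a difference of 5.

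A second defence is that more than 1 df is not in itself an error. The sentence names interactions as well as main effects, and one of the trial's main goals is to find variables associated with variability in the effect. This also stands. What remains is that 5 df matches no effect that the section, the hypotheses or the analysis plan describes.

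A third is that the group comparison is sized separately and the authors recruit to the largest figure. That is fair. A reader might infer that the trial is underpowered or that 96 must change. Step 3 shows the opposite for the arm comparison: power at 86 is above 95% for every effect size derived from the section.

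Finally, f = 0.40 with 5 df gives 80.1% power at 86, so a reader might infer that 86 is an 80%-power figure. The section states 90%, and nothing in it supports that reading over the 5.5-point route.

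**Conclusion.** The point holds as an inconsistency in the calculation that sets the sample size. The statement that 86 uses the same effect size as the totals before it cannot be true: 68 matches f = 0.40, 46 needs f of about 0.49 to 0.50, and 86 needs f of about 0.453 to 0.458. The 86 also rests on a 5-df test that is not defined and is not the two-arm contrast. The t-test total of 46 is itself too small for its printed inputs, which need 64.

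If the 5-df test were truly intended with the printed 5-point difference, 86 would give 83.7% power and not 90%. For the primary comparison there is no shortfall: about 97% power for 5 points, or 90% for about 4.2 points.

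These figures assume that SD 6 applies to the score analysed, that 86 of 96 patients are evaluable, and that f = 0.40 is what the section means by a large effect. The severity is moderate: the basis of the target is wrong as written, but the target is adequate for the primary outcome.

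**What to change.** Keep N = 96 and restate its basis with one effect size for the primary contrast (arm difference in MADRS change to the tenth session, 1 df). Suggested wording: *96 randomised patients, 86 evaluable after 10% drop-out, give about 97% power for a difference of 5 points (SD 6), or 90% power for about 4.2 points, two-sided alpha 0.05.*

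Correct the t-test total to match the chosen effect: 64 for 5 points or 54 for 5.5 points. If the ANCOVA sentence stays, give its numerator df, the effect it tests and the f used, and remove the claim that the effect size is the same.

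The cost is wording only. Recruitment, design and analysis do not change.

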### ITBS interventions

Stimulation will be performed with a Mag & More PowerMag EEG 100 system (https://magandmore.com) with a double PMD70 p-cool (fluid-cooled) figure-eight coil. Sham stimulation will be performed with a double PMD70 p-cool figure-eight sham coil. The sham coil has an identical look, weight and sound compared to the true coil and delivers electrical stimulation that can be felt on the skin but without penetrating the skull.

A high-resolution T1-weighted image obtained at baseline will be used for real-time MRI-guided neuronavigation for optimal coil positioning. A Localite TMS-navigator system (https://www.localite.de) will be used for the determination of the target area [54] in MNI-space (*X* =  − 38, *Y* = 44, *Z* = 26) within the left DLPFC prior to the first day of stimulation. Additionally, we will use the Beam F3 method [55] for comparison with the stimulation point found by the neuronavigation [56]. The stimulation point on the scalp obtained by neuronavigation will be recorded with the coordinate system used in the Beam F3 method for use in stimulation sessions 2–10.

iTBS will be delivered with the same parameters as in Blumberger et al. [4] with stimulation intensity at 120% of resting motor threshold (RMT) triplet 50 Hz bursts repeated at 5 Hz; 2 s on and 8 s off, 600 pulses per session with a total duration of 3 min 9 s.

RMT is determined by observable right-handed thumb twitches (musculus abductor pollicis brevis) in three of five trials while delivering stimulation to the left primary motor cortex [57]. If a patient reports that stimulation intensity at 120% of RMT is intolerable at the first stimulation, the stimulation intensity will be titrated from 100% on day 1 to 120% on day 3. RMT will be determined prior to each stimulation, making sure not to stimulate above the suprathreshold intensity of 120% [58]. ITBS or sham stimulation will be provided once a day for 10 days for two consecutive weeks (except Saturdays and Sundays). Each patient will start treatment at approximately the same time between 9 am and 3 pm during the 10-day treatment period. All iTBS procedures, including RMT assessment, will be performed by trained personnel not blinded to the study condition. Participants will be monitored by study staff for 10 min after the stimulation and can thereafter leave the study site. The trial adheres to the latest safety recommendations for rTMS [36, 37].

A structured form will be used to document the side effects after each day of iTBS. Any side effects will be documented in the individual’s file. An analysis of side effects will be reported in the publication.

The criteria for discontinuing or modifying allocated interventions for a given participant include the following: worsening of disease, report of adverse side effects, withdrawal of consent, change in drugs or not receiving stimulation on more than 2 days. If the patient is absent from one or two stimulations, these will be added to the treatment schedule. For safety reasons, participants will be asked about sleep, alcohol, illegal drugs and medication use prior to each simulation. Participants will be asked about their well-being prior to and after each iTBS stimulation. The participants will be asked to drink no more than one unit of alcohol the night before stimulation. If the patient reports drinking more alcohol, stimulation will be postponed to the day after. Stimulation will also be postponed if the participant reports significant tiredness and/or lack of sleep the night before.

### Statistical analysis plan

Descriptive analyses of the data collected during each patient’s evaluation will be conducted up until the final evaluation. The time points for analyses are after the 5th iTBS session, 10th iTBS session and 4 weeks after the last stimulation. The follow-up 4 weeks after is used to test the stability of the reduction in depressive symptoms after iTBS and the change in symptoms after sham treatment. The effect of the intervention will be assessed as the linear change in depression scores measured on the MADRS and BDI-II.

Single means (e.g. baseline data) will be analysed with statistical methods within the framework of general linear models (GLMs) (ANOVA, linear regression, Pearson correlation, *t*-tests) if the statistical assumptions for GLMs are met. In the case of nonnormal data, nonparametric statistics will be performed. Changes in quantitative data over time will be analysed by linear mixed models (LMM), which allow for a combination of fixed and random effects. LMM estimates the parameters using all available patient data, is thus less sensitive to missing data, and has flexible modelling options for the residual covariance structure of the data [49].

Analyses of brain imaging data will be performed in separate programs according to the type of data. FreeSurfer (FS) [59] (https://surfer.nmr.mgh.harvard.edu/) will be used for the preprocessing of structural imaging data, and permutation analysis of linear models (PALM) will be used to perform statistics on structural data preprocessed in FS and in analyses where imaging data are combined with other data as covariates or factors [60]. Statistical Parametric Mapping 12 (https://www.fil.ion.ucl.ac.uk/spm/software/spm12/) will be used for the preprocessing of functional MRI data, and GIFT (https://www.nitrc.org/projects/gift) will be used for independent component analyses (ICA) and statistical analyses of rs- fMRI.

Missing data will be described for each group at all time points of measurement, and imbalances will be evaluated. Missing data will not be imputed in the analyses. Any patient who drops out will be described according to group, exit date, exit reason, characteristics at inclusion and last data collected.

An alpha value of 0.05 will be used for all analyses, and Bonferroni corrections will be applied when appropriate for controlling the type 1 error rate.

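### The primary mixed model for MADRS change is not tied to baseline MADRS or to the stratifier sex, and its most natural form may give a less precise treatment contrast than the data allow

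*Protocol article*

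**What the plan says.** The section on primary outcome variables fixes the endpoint: "The primary outcome variable is the change in the level of depressive symptoms measured with the clinician-rated MADRS", taken from baseline to after ten stimulations. The section headed Statistical analysis plan adds "The effect of the intervention will be assessed as the linear change in depression scores measured on the MADRS and BDI-II" and names the tool: "Changes in quantitative data over time will be analysed by linear mixed models (LMM), which allow for a combination of fixed and random effects". It lists no fixed effects, whether arm, visit or covariates.

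The section on sample size presents the LMM as the replacement for repeated ANOVA, chosen because it copes better with randomly missing data, and treats the two as comparable for sizing. The repeated ANOVA there is labelled pre-post. The same section takes its largest sample size from an ANCOVA-like calculation, "assuming 2 groups and 3 covariates will require group sizes of 43", and does not name the three.

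The section on secondary outcomes and covariates says: "Other covariates are participant characteristics (age, sex) and depression characteristics (treatment refractoriness, symptom severity". These stand next to the genetic and MRI measures, with no statement of which model uses which variable. On randomization, the article says that "the groups will be stratified by gender in the randomization".

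**The concern.** In a two-arm pre-post repeated ANOVA, the arm-by-time test compares mean change scores, and each arm has its own baseline mean. An LMM built as its counterpart does the same unless it is told otherwise. Randomization makes the true baseline means equal, so a model that leaves them free discards information. The result is an avoidably wide interval around the main estimate, and chance baseline imbalance is handled less well than it could be.

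The covariate list does not settle the matter. If symptom severity means baseline MADRS and it is added to a model that also has baseline MADRS as an outcome, the same measurement sits on both sides. The contrast is still a difference in change.

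**Working it through.** **The plan's own figure.** Inputs from the sample size section: baseline mean 22, changes of 42% and 17%, pooled SD 6, alpha 0.05, power 0.9, three covariates. The unrounded difference is 22 × (0.42 − 0.17) = 5.5, so f = (5.5/6)/2 = 0.458. A noncentral F with λ = f²N, 5 numerator df and N − 2 − 3 denominator df gives N = 85, or 86 with equal groups, and a critical F of 2.33. This matches the article. Then 86/0.9 = 95.6, rounded up to 96, also matches. The calculation gives the covariates no variance reduction. The 1-df arm effect with three covariates needs only 53 in total at 5.5/6, or 63 at 5/6. The planned N therefore does not rely on adjustment.

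**The two contrasts.** Let s0 and s1 be the SDs at baseline and after session 10, ρ their correlation, and 43 the number per arm.

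- Difference in change: V_c = s1² + s0² − 2ρ·s1·s0
- Baseline-adjusted: V_a = s1²(1 − ρ²)
- SE = √(2V/43)
- V_c − V_a = (s0 − ρ·s1)², which is never negative and is zero only when ρ = s0/s1

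The article attaches the SD of 6 to the post-treatment comparison (13 versus 18). It gives neither s0 nor ρ. Both are assumptions here: ρ from 0.3 to 0.7, and s0 of 6, 4 or 3. The lower values reflect the entry floor of 20, the assumed baseline mean of 22 and the exclusion of severe episodes requiring inpatient treatment.

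| s0 | ρ | V_c | V_a | V_a/V_c | Reduction |
|---|---|---|---|---|---|
| 6 | 0.3 | 50.4 | 32.76 | 0.65 | 35% |
| 6 | 0.5 | 36.0 | 27.00 | 0.75 | 25% |
| 6 | 0.7 | 21.6 | 18.36 | 0.85 | 15% |
| 4 | 0.3 | 37.6 | 32.76 | 0.87 | 13% |
| 4 | 0.5 | 28.0 | 27.00 | 0.96 | 4% |
| 4 | 0.7 | 18.4 | 18.36 | 1.00 | 0% |
| 3 | 0.3 | 34.2 | 32.76 | 0.96 | 4% |
| 3 | 0.5 | 27.0 | 27.00 | 1.00 | 0% |
| 3 | 0.7 | 19.8 | 18.36 | 0.93 | 7% |

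With s0 = 6 the SEs at ρ = 0.3, 0.5 and 0.7 are 1.53, 1.29 and 1.00 for change, against 1.23, 1.12 and 0.92 adjusted. At ρ = 0.5 the 95% half-width goes from 1.96 × 1.294 = 2.5 points to 1.96 × 1.121 = 2.2 points.

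**Dependence on parameterisation.** Generalised least squares for an LMM with free arm means at baseline reproduces the change-score SEs (1.53, 1.29, 1.00). The same LMM with one common baseline mean gives exactly the adjusted SEs (1.23, 1.12, 0.92).

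**Severity as a main effect only.** A time-constant term shifts every visit of a patient equally, so it cancels from within-patient change. With complete data the arm-by-time contrast stays the change-score contrast.

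**Power.** For a difference of 5 with 43 per arm and s0 = 6, power is 0.898, 0.969 and 0.999 unadjusted, against 0.980, 0.993 and above 0.999 adjusted. With s0 of 3 or 4, V_c is at most 37.6, below the 50.4 that gives 0.898, so the lowest unadjusted power is higher still.

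**Sex.** If sex explains a share R² of outcome variance, the SE is multiplied by √(1 − R²). For an assumed R² of 0 to 0.05 this is 1.000 to 0.975, a gain of at most 2.5%.

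**The case against.** The strongest reply is that this is silence, not error. A journal article condenses the plan, and the analysis section names no fixed effects of any kind. The absence of baseline MADRS and sex there does not exclude them, and both sex and symptom severity appear in the covariate list. The loss depends on a parameterisation that the article does not state: a common baseline mean, or a change score adjusted for baseline, has no loss. An SD of 6 at baseline is not the plan's figure and sits poorly with a floor of 20 and a mean of 22.

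Most of this stands. It removes three stronger readings that a reader might infer:

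- **That the plan leaves baseline and sex out of the primary model.** No section says so.
- **That three covariates in the sizing contradict the four listed.** Three is a setting in one of several power calculations, and the listed covariates serve work packages reported in separate articles.
- **That the sample size depends on an adjustment that the analysis then drops.** The figure of 86 assumes no gain from covariates.

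One point remains. The article is not neutral on the form of the model: it defines the effect as change and introduces the LMM as the counterpart of a pre-post repeated ANOVA. The natural reading has free baseline means, and no section describes the constraint or adjustment that would avoid the loss.

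**Conclusion.** The concern holds in a limited form. The primary analysis is worded so that its most natural version is a difference in change scores, and the listed covariates are not connected to it. In that version the variance of the main contrast exceeds what baseline adjustment would give.

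The size rests on two quantities that the article does not supply, so no single figure should be quoted. The 15% to 35% range needs a baseline SD as large as the post-treatment one. The 0% to 13% range, for a baseline SD of 3 to 4, fits the entry criteria better. The formulas take change as baseline to session 10, with complete data.

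A certain loss of precision, or an underpowered trial, would be too strong a conclusion. At 43 per arm and a difference of 5, power is about 0.90 or more throughout the range examined. Leaving out sex would make the reported SE slightly too large, which is a conservative error.

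**What to change.** State the primary model in the section headed Statistical analysis plan:

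- **Outcomes:** MADRS after session 5, after session 10 and at 4 weeks.
- **Fixed effects:** arm, visit, arm by visit, baseline MADRS, baseline by visit, and sex as the stratification factor.
- **Primary contrast:** the arm difference after session 10.
- **Baseline MADRS:** used as a covariate only. An LMM that keeps baseline as an outcome with a common mean across arms is equivalent in precision and would serve as well.
- **Remaining covariates:** age, treatment refractoriness, genetic and MRI measures assigned to the predictor hypotheses.

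All these variables are already collected. The cost is a few degrees of freedom and a short change of wording. The sample size need not change.

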### Objectives, hypotheses and trial design

The present trial is a single-centre, parallel-group, superiority, double-blind randomized controlled trial examining the effect of once-a-day iTBS compared to sham iTBS for 10 consecutive workdays in outpatients with moderate, unipolar depression. The main goals are to evaluate the effectiveness of 2 weeks of iTBS over the dorsolateral left DLPFC for the reduction of depression symptoms and to identify variables associated with the variability in the effect of iTBS on depressive symptoms. The main hypotheses of the trial are as follows:

(1) Patients receiving iTBS will display significantly larger reductions in depressive symptoms measured by the Montgomery-Aasberg Depression Rating Scale (MADRS) [33] and Becks Depression Inventory II (BDI-II) [34] compared to patients receiving sham stimulation. (2) Reduction in depressive symptoms will be significantly associated with a concomitant improvement in executive functions measured by neuropsychological tests. (3) Stronger connectivity at baseline between the DLFPC and the anterior cingulate cortices will be associated with better response to iTBS. (4) Variability in genetic measures will be significantly associated with treatment response to iTBS. (5) Variability in white matter structural measures of the brain will be significantly associated with the anti-depressive response to iTBS. The hypotheses will be investigated in separate work packages and will be reported in separate scientific articles.

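### Where a family of tests is corrected, Holm's step-down procedure should replace Bonferroni: same family-wise error, never fewer rejections (an efficiency gain, not an error)

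*Protocol article*

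**What the plan says.** The section Statistical analysis plan sets the level and the correction in one sentence: "An alpha value of 0.05 will be used for all analyses, and Bonferroni corrections will be applied when appropriate". It names no other procedure and does not say which tests form a family.

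Executive function is the clearest place where several tests bear on one domain:

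- Secondary outcome variables and covariates: "Secondary outcome variables are changes in anxiety, executive functions and quality of life from baseline to after the 10th stimulation".
- Objectives, hypotheses and trial design, hypothesis 2: "Reduction in depressive symptoms will be significantly associated with a concomitant improvement in executive functions measured by neuropsychological tests".
- Schedule of enrolment, interventions and assessments, in the text after Table 1: "Aspects of executive functions will be assessed with selected subtests from the Colour-Word Interference Test, the Verbal Fluency Test and the Trail Making Test", "and with the Wisconsin Card Sorting Test". That makes at least four performance tests. The BRIEF-A "will be used to assess patient-reported dysexecutive problems in everyday life", and the N-back task "will be used to measure reaction time, attention and working memory".

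No expected cognitive effect size, no correlation between the tests and no power figure for executive function is given.

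**The concern.** Bonferroni compares every p-value in a family of m tests with 0.05/m, even after some hypotheses have been rejected. Holm relaxes the threshold after each rejection and keeps the same guarantee. When several tests of one domain are all affected, Bonferroni will therefore leave some of them non-significant that Holm would have declared, with nothing gained in return. At stake is how many individual secondary results the trial can claim. The primary MADRS comparison is a single test and is not touched.

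**Working it through.** **Inputs from the protocol article.** Two-sided alpha 0.05. Groups of 43, 86 in total (Sample size calculation). The recruitment target reproduces: 86/0.9 = 95.6, rounded up to 96. It was derived for depression scores, so 43 per arm serves here only as the evaluable number.

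**Assumptions not in the documents.** m = 4 tests (5 with the BRIEF-A, 7 with N-back and digit span as well), the same standardised effect d = 0.4 or 0.5 on each test, and an inter-test correlation of 0.3 to 0.5.

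**Step 1: Holm against Bonferroni, by argument.** Order the p-values. Holm compares the i-th smallest with 0.05/(m − i + 1) and stops at the first failure. For m = 4 the thresholds are 0.05/4 = 0.0125, 0.05/3 = 0.0167, 0.05/2 = 0.025 and 0.05. Bonferroni uses 0.0125 throughout. No Holm threshold is below 0.0125, so whatever Bonferroni rejects, Holm rejects too.

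For the error rate, let m0 hypotheses be true. A first false rejection requires the smallest of their m0 p-values to be at most 0.05/m0. By the union bound this has probability at most m0 × 0.05/m0 = 0.05, whatever the dependence. In simulation with no true effects, the family-wise error of both procedures was 0.033 to 0.048.

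**Step 2: Bonferroni power for one test (normal approximation).** The noncentrality is d × √(43/2), and the two-sided critical value at 0.0125 is 2.498.

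- d = 0.4: 0.4 × 4.637 = 1.855; Φ(1.855 − 2.498) = Φ(−0.643) = 0.26.
- d = 0.5: 0.5 × 4.637 = 2.318; Φ(2.318 − 2.498) = Φ(−0.180) = 0.43. The exact t calculation gives 0.41.

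**Step 3: Holm, by simulation, m = 4, equal effects.**

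| | Bonferroni | Holm |
|---|---|---|
| d = 0.4, average per test | 26% | 31% |
| d = 0.5, average per test | 41–43% | 49–51% |
| d = 0.4, at least one test | 54–60% | same |
| d = 0.5, at least one test | 74–80% | same |

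In the first two rows the normal approximation gives the higher end of any range and t-tests the lower. In the last two rows the range comes from the correlation. At correlation 0.5 and d = 0.5, t-tests give 38% against 46% for m = 5, and 34% against 42% for m = 7.

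The at-least-one rows agree because Holm's first threshold is Bonferroni's. For the same reason the gain nearly vanishes when only one test is affected: with d = 0.6 on one of four tests and correlation 0.5, power for that test is 0.59 with Bonferroni and 0.60 with Holm.

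**Step 4: a composite, for comparison.** One equal-weight composite was tested at 0.05, with m = 4, correlation 0.5 and t-tests.

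| True pattern | Bonferroni | Composite |
|---|---|---|
| d = 0.5 on all four (at least one rejected) | 0.73 | 0.83 |
| d = 0.6 on two of four (at least one rejected) | 0.77 | 0.42 |
| d = 0.6 on one of four (that test rejected) | 0.59 | 0.14 |

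The composite gains in the first pattern and loses heavily in the other two.

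**Step 5: hypothesis 2.** It concerns an association, so the two-arm figures above do not measure its power. The argument in Step 1 applies to any set of p-values and so covers it.

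**The case against.** The strongest reply is that nothing is wrong: Bonferroni is valid, and preferring Holm is a matter of efficiency. That stands, and the point is offered only as such.

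It can also be said that the plan never states that Bonferroni will be applied across the executive tests, only where judged appropriate. That stands too, so the loss on this outcome is conditional. Which tests form the family, and which score leads, are details that an article may leave to a fuller plan that is not shown. Their absence is not a finding.

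Three stronger readings are tempting, and the documents do not support them:

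- *Hypothesis 2 could be declared confirmed by any one test at 0.05.* The text sets no such rule.
- *Holm restores the power to show an executive effect at all.* It adds nothing to the chance of a first rejection. Its benefit lies in how many tests are shown.
- *A composite is the better analysis because executive function is a single outcome.* The article uses the plural and speaks of aspects, so separate facets are a legitimate target. A composite answers a different question, and its advantage reverses when effects are uneven. The subtests that would enter it are not identified either.

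Finally, Bonferroni has simple simultaneous confidence intervals that match its tests, and Holm does not do so directly. This is a real but small cost.

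**Conclusion.** The point holds as an improvement to a stated method. That Holm is never worse than Bonferroni in rejections, at equal family-wise error, is a matter of proof and needs no assumption about effects or correlations. The size of the gain does rest on assumptions. With four tests, equal effects, correlation 0.3 to 0.5 and 43 per arm, it is about 5 percentage points of average per-test power at d = 0.4 (26% to 31%) and about 8 at d = 0.5 (42% to 50%). It is close to nil if only one test is affected. The validity of the plan and the primary analysis are unaffected.

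**What to change.** In the Statistical analysis plan, name Holm's step-down procedure instead of Bonferroni, for example: *within each family of hypotheses, p-values will be adjusted by Holm's procedure at a family-wise level of 0.05.* Only the analysis wording changes; data collection and sample size stay as they are. Where simultaneous intervals are wanted, Bonferroni intervals can still be reported, with a note that they may be wider than Holm's decisions imply.

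A lead executive composite is optional. If the investigators expect a broad effect, they can prespecify one before unblinded analysis, stating which subtest scores enter it, their direction and their scaling, with the single tests reported under Holm. If they expect effects on particular facets, they should keep the separate tests.
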